### **2.2 Primary Objective and Outcome measures**

The primary objective is to evaluate the effectiveness of tPCS in addition to standard therapy in improving social functioning in children with ASD, aged 3 to 14 years old. The primary outcome measure will be the change in mean scores as measured by the Autism Treatment Evaluation Checklist (ATEC), for both ATEC total and subdomain scores, at post-treatment compared to baseline. The secondary outcome measure will be the change in mean scores as measured by the Autism Behaviour Checklist (ABC), for both ABC total and subdomain scores, at post-treatment compared to baseline.

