### Autism Treatment Evaluation Checklist (ATEC)

ATEC is developed by the Autism Research Institute and designed as a one-page checklist. Comprising 77 items, the ATEC has been utilized to assess the efficacy of interventions by measuring changes in response to various treatment modalities for children with ASD. The ATEC consists of four subscales totaling 77 items:

- Scale I: Speech, Language, and Communication (14 items, with scores ranging from 0 to 28)
- Scale II: Sociability (20 items, with scores ranging from 0 to 40)
- Scale III: Sensory and Cognitive Awareness (18 items, with scores ranging from 0 to 36)
- Scale IV: Health, Physical Condition, and Behavior (25 items, with scores ranging from 0 to 75)

Each category within the ATEC utilizes a four-point rating scale to gauge the severity of issues, ranging from 0 (indicating no problem) to 3 (indicating a serious problem). The ATEC generates a total score ranging from 0 to 179, with higher scores indicating a greater degree of reported activity limitations. This comprehensive assessment tool enables researchers and clinicians to gain insight into the challenges faced by individuals with ASD and to monitor changes in symptoms and functioning over time. For this study, the ATEC will be administered twice (pre- and post-tPCS) and carried out by an experienced therapist or doctor who is blinded regarding the subject allocation.

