## 9 Sample Size and Statistical Methods

### 9.1 Determination of Sample Size

Based on a two-sided paired t-test at 80% power, 5% one-sided alpha and an expected effect size of small (0.20) when using bilateral frontal montage and medium (0.52) when using prefrontal-cerebellar montage, we will use an average of 0.36 effect size to compute the sample size, which leads to 120 per group. Based on an estimated 40% drop-out rate due to potential implications from post- COVID heightened travelling restrictions in Guangdong province, a sample size of 339 is required. We will use 340 as the sample size for recruitment in this study.

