### 9.2 Statistical and Analytical Plans

#### 9.2.1 General Considerations

Statistical analysis will be implemented using the IBM SPSS version 27.0. Before applying any statistical test, the data sets will be tested for a normal distribution with the Shapiro–Wilk test. If the data was found to be normally distributed, then one- way analysis of variance ANOVA and Student’s t-test will be used for the comparison between groups. Analysis of Covariance ANCOVA will be used to compare one or more means between groups

while controlling for the effects of one or more covariates (continuous variables that are related to the dependent variable). For comparison with the baseline value, paired t-test or one-way analysis of variance (ANOVA) will be used to compare the differences within the group before and after treatment. If the data was found to be not normally distributed then Kruskal-Wallis test or Mann-Whitney rank-sum test was used for the comparison. In order to correct for multiple comparisons, Bonferroni correction will be used to further validate the significance of each p-value. All statistical tests were conducted using a two-sided test. The  $\alpha$ -value was set to 0.05 for all the statistical tests and < 0.01 for Bonferroni correction. Chi-Squared test was used for categorical data, and Mann-Whitney rank sum test was used for ordinal data.

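### All five ATEC scores are primary, and the plan does not say whether 0.05 or 0.01 decides success; the 80% power applies only to one score tested at 0.05

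*Combined protocol and SAP*

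**What the plan says.** Section 2.2 sets the primary outcome as a shift in the group averages, "as measured by the Autism Treatment Evaluation Checklist (ATEC), for both ATEC total and subdomain scores, at post-treatment compared to baseline". The ATEC note under section 4.3 states that "The ATEC consists of four subscales totaling 77 items". The total and four subdomains therefore share primary status. No lead score, testing order or definition of a positive trial is given. Appendix 5, section A5.3, repeats the total and the subdomains as primary for the interim analysis.

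On thresholds, section 9.2.1 says that alpha "was set to 0.05 for all the statistical tests and < 0.01 for Bonferroni correction", and that "Bonferroni correction will be used to further validate the significance of each p-value". It adds that "All statistical tests were conducted using a two-sided test". It names neither the family of tests behind the 0.01 nor the threshold that governs the primary conclusion.

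Section 9.1 opens its calculation with "Based on a two-sided paired t-test at 80% power, 5% one-sided alpha". It uses an effect size of 0.36, reaches 120 per group, and then allows for 40% drop-out. It does not mention 0.01 or more than one primary score.

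**The concern.** Suppose one ATEC subscale gives p = 0.03 and the other four scores do not reach 0.05. Under the 0.05 sentence that is a positive primary result; under the 0.01 sentence it is not. Nothing in the plan settles which applies, so both the deciding score and the deciding threshold could be chosen after the data are seen.

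The two readings fail in different ways. Five chances at 0.05 raise the risk of a false positive primary finding above 5%. A strict 0.01 controls that risk, but the sample size was not calculated for it, so the stated power does not describe the test that would be run.

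**Working it through.** **Inputs.** Effect size 0.36 (SD = 1), 120 per group, 80% power and 40% drop-out come from section 9.1. The 170 randomised per arm come from section 4.2, and the 30% to 40% drop-out range from the Protocol Deviations text. The four subscales, with maxima 28, 40, 36 and 75 summing to 179, come from the ATEC note. The thresholds 0.05 and 0.01 come from section 9.2.1.

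**1. Reproduce the plan's 120 per group.** For a two-sample, two-sided comparison at 0.05:

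n = 2(1.960 + 0.842)² / 0.36² = 121.1, so 122 per group.

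That is close to the stated 120. The alternatives suggested by the wording of section 9.1 do not come near it:
- two-sample, one-sided 0.05: 96 per group
- paired, two-sided: 61 to 63
- paired, one-sided: 48 to 50

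So 120 is, in effect, one two-sided between-group comparison at 0.05.

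**2. Family-wise error if 0.05 decides on any score.** The ATEC total is the sum of its subscales, so the five tests cannot be independent. I therefore rely on a simulation (1,000,000 draws) of four equally correlated subscale statistics and their standardised sum under no treatment effect. The correlations are assumptions.

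| Correlation between subscales | Any of five at 0.05 | Any of five at 0.01 |
|---|---|---|
| 0 | 20.4% | 4.6% |
| 0.3 | 18.0% | 4.1% |
| 0.5 | 15.8% | 3.7% |
| 0.7 | 13% | 3.0% |
| 0.9 | 9.4% | 2.1% |

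Weighting the total by the subscale maxima changes these figures very little (20.2% at zero correlation). At 0.01 the Bonferroni bound is 5 × 0.01 = 5% whatever the correlation.

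**3. Power for one named score if 0.01 decides.** The normal approximation is power = Φ(0.36 × √(n/2) − 2.576). The t-test value is beside it.

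| Analysed per arm | Basis | Normal approximation | t-test |
|---|---|---|---|
| 120 | section 9.1 | Φ(2.789 − 2.576) = 58.4% | 57.7% |
| 119 | 340 × 0.70 / 2 | 58.0% | 57.2% |
| 102 | 340 × 0.60 / 2 | Φ(2.571 − 2.576) = 49.8% | 49.0% |
| 170 | no loss | Φ(3.319 − 2.576) = 77.1% | 76.6% |

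**4. Number needed for 80% power at 0.01.** n = 2(2.576 + 0.842)² / 0.36² = 180.2, so 181 analysed per arm. The trial randomises 170.

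**The case against.** The strongest reply is that section 9.2.1 does plan a correction. Read naturally, 0.05 is the nominal level and 0.01 is the corrected one. Since 0.05/5 = 0.01, that fits five ATEC scores and holds their family-wise error at or below 5%. This largely stands, and it would be wrong to say that the plan has no multiplicity control. But the section never links 0.01 to the ATEC family, and the same figure fits the five ABC subscales equally well. A step meant to further validate p-values is not plainly a binding one.

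A reader might infer three stronger things that the documents do not support.

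- *That family-wise error is as high as 22.6%.* That is 1 − 0.95⁵, which needs five independent tests. The total is built from the other four scores, so this cannot occur; about 20% is the figure at zero correlation.
- *That 5% error and 80% power can never hold together.* The plan does not define success. If any one score at 0.01 sufficed and every score had an effect of 0.36, power at 120 per arm would be 91% at correlation 0.3, 80% at 0.7 and 71% at 0.9, with error within 5%. Section 9.2.1 also lists ANCOVA. If 0.36 is standardised on the raw-score SD and the baseline correlation is 0.5, 0.6 or 0.7 (both assumptions), power for one score at 0.01 is about 73%, 81% or 90% at 120 per arm, and 64%, 73% or 84% at 102. Section 9.1 relies on neither route, but neither is excluded.
- *That a result on ATEC total cannot bear on social functioning,* because Sociability is 40 of 179 points (22%). Share of score range is not share of variance or of treatment response. This is a debatable question of construct, separate from multiplicity.

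The 102 per arm also assumes that only completers are analysed at 40% loss. Section 3.8 intends best-effort assessment and imputation, so the analysed number could be larger. That is why the range up to 170 is shown.

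**Conclusion.** The point holds. Five scores are primary, two thresholds are stated, and no rule says which score or threshold decides. The sample size rests on one comparison at 0.05.

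If any score at 0.05 counts, family-wise error is roughly 9% to 20% for subscale correlations from 0.9 down to 0. If 0.01 governs, error across the five scores is controlled, but an unadjusted two-sample t-test on a named score such as ATEC total has about 49% to 58% power at 102 to 120 per arm. Even with no loss it has 77%. These powers take the plan's 0.36 at face value.

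The defect is an undefined decision rule and a sample size that does not match one of its two readings. It does not show that the trial must fail on error or on power.

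**What to change.** - **Section 2.2:** name change in ATEC total at post-treatment as the single primary outcome, tested at two-sided 0.05 less any alpha spent at the interim analysis.
- **Sections 2.2 and 2.3:** make the four ATEC subdomains, ABC total and CSHQ total secondary, in one stated order or under Holm. Put Sociability first in a fixed order, because the objective is social functioning. Treat ABC and CSHQ subdomains as descriptive.
- **Section 9.2.1:** replace the flat 0.01 sentence with this rule.
- **Appendix 5, section A5.3:** align the interim text, which still lists total and subdomains as primary.

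The cost is wording, with no added participants or visits. The downside is that subscale results become secondary claims. The change restores the single-comparison basis of the 120 per group (79% power by t-test at two-sided 0.05). It does not cure attrition: at 102 per arm, power at 0.05 would still be about 73%.

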### **2.3 Secondary Objective and Outcome measures**

The secondary objective is to assess the effectiveness of tPCS in addition to standard therapy in improving sleep disorders in children with ASD, aged 3 to 14 years old. This secondary outcome measure will be the change in mean scores of the Children's Sleep Habits Questionnaire (CSHQ), for both CSHQ total and subdomain scores, at post-treatment compared to baseline.

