## **2 Hypothesis and Objectives**

### **2.1 Hypothesis**

tPCS, in addition to standard behavioural therapy, will improve social functioning compared to standard therapy alone in children with ASD aged 3 to 14 years old. We also hypothesize that tPCS will improve sleep disorders in children with ASD aged 3 to 14 years old when compared to standard behavioural therapy alone.

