### **4 Children's Sleep Habits Questionnaire (CSHQ)**

The Children's Sleep Habits Questionnaire (CSHQ) is a retrospective assessment tool to investigate sleep patterns in young children consisting of 45 items designed for parents to report on their child's sleep behavior. The CSHQ covers various sleep domains, including bedtime behavior and sleep onset; sleep duration; anxiety around sleep; behavior occurring during sleep and night wakings; sleep-disordered breathing; parasomnias; and morning waking/daytime sleepiness. Each item is rated on a three-point scale: "usually" if the behavior occurred five to seven times per week, "sometimes" for two to four times per week, and "rarely" for zero to one time per week. In this study, the CSHQ will be administered twice (pre- and post-tPCS) by experienced therapists who is blinded regarding the subject allocation through interviewing parents or caregivers in clinic.

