## **A5.3 Statistical interim analyses:**

Primary outcome measure: Autism Treatment Evaluation Checklist (ATEC) total and subdomain scores will be used for analysis of change in social functioning. T-tests, ANOVA and ANCOVA will be used to examine the rate of improvement for these scores. Scores will be compared with baseline. Estimates of the difference in the average rate of improvement in the scores will be obtained. These estimates will then be tested against the null value of no difference between both groups.

Secondary Outcome measures: Autism Behaviour Checklist (ABC) total and subdomain scores will be used for analysis of change in social functioning. The Childhood Sleep Habits Questionnaire (CSHQ) will be used for analysis of change in sleep functions. Scores will be compared with baseline. Estimates of the difference in the average rate of improvement in the scores will be obtained. These estimates will then be tested against the null value of no difference between both groups.

Participant characteristics at baseline (including demographic and clinical) will be compared within each group using independent sample t-tests or chi-square test as appropriate for the variable.

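### The sleep hypothesis and the secondary ABC outcome each rest on a total plus all subdomain scores, with no deciding score and a Bonferroni step whose family and role are undefined

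*Combined protocol and SAP*

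**What the plan says.** - **Sleep.** Section 2.1 states sleep as a hypothesis of its own: "We also hypothesize that tPCS will improve sleep disorders in children with ASD aged 3 to 14 years old". Section 2.3 measures it on the CSHQ, "for both CSHQ total and subdomain scores, at post-treatment compared to baseline". The CSHQ note under section 4.3 lists seven domains: "bedtime behavior and sleep onset; sleep duration; anxiety around sleep; behavior occurring during sleep and night wakings; sleep-disordered breathing; parasomnias; and morning waking/daytime sleepiness". The wording presents that list as open-ended, and the form in Appendix 3 has five headed blocks of items (bedtime, sleep behaviour, night waking, morning waking, daytime sleepiness).
- **ABC.** Section 2.2 makes the ABC a secondary outcome under the social-functioning objective, "for both ABC total and subdomain scores". The ABC note under section 4.3 and Appendix 2 both give five subscales.
- **Error control.** Section 9.2.1 says "All statistical tests were conducted using a two-sided test", that alpha "was set to 0.05 for all the statistical tests and < 0.01 for Bonferroni correction", and that "Bonferroni correction will be used to further validate the significance of each p-value".
- **Interim.** Section A5.3 applies between-group tests to the ATEC, ABC and CSHQ: "These estimates will then be tested against the null value of no difference between both groups". It names no deciding score for the ABC or the CSHQ.

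No section makes a CSHQ or ABC claim conditional on ATEC, orders the two scales, or labels any subdomain exploratory.

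**The concern.** The sleep hypothesis can be called supported on the CSHQ total or on any one subdomain, and the ABC outcome likewise, whatever ATEC shows. The only protection is the Bonferroni sentence. It leaves open how many tests are counted and whether a result with p between 0.01 and 0.05 counts as a finding or as one that failed validation.

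An analyst who lets 0.05 decide and an analyst who lets 0.01 decide can both say that they followed the plan. A reader of the results could not tell a planned sleep claim from one selected among several scores. Because sleep is one of the trial's two stated hypotheses, this matters more than it would for a list of supportive outcomes.

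**Working it through.** **Inputs from the documents.** Two-sided tests at 0.05, with a Bonferroni check at < 0.01 (9.2.1). ABC: 5 subscales + 1 total = 6 scores. CSHQ: 7 listed domains + 1 total = 8 scores, on the assumption that the listed domains are the subdomains. Total 6 + 8 = 14.

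**Input that is assumed.** The correlation between test statistics is not in the documents. I use a common value of 0.5, with a range of 0 to 0.8.

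**The plan's own figure.** The plan states no error rate for the secondary claims. Its only multiplicity figure is 0.01, which is reproduced by 0.05/5. That matches the five ATEC scores (4 subscales + total). Other families would need:
- 6 ABC scores: 0.05/6 = 0.0083
- 8 CSHQ scores: 0.05/8 = 0.00625
- all 14: 0.05/14 = 0.0036

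**Error rates with no true effect on any score, single final analysis.** For k independent scores at level a:
- either direction: 1 - (1 - a)^k, so for k = 14: 1 - 0.95^14 = 51.2% and 1 - 0.99^14 = 13.1%
- benefit only: 1 - (1 - a/2)^k, so for k = 14: 1 - 0.975^14 = 29.8% and 1 - 0.995^14 = 6.8%

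For k scores with common correlation r and critical value c (1.960 at 0.05, 2.576 at 0.01), the either-direction rate is 1 minus the average, over a standard normal u, of [Phi((c - sqrt(r)u)/sqrt(1-r)) - Phi((-c - sqrt(r)u)/sqrt(1-r))]^k. For benefit only, drop the second Phi term.

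| Scores | Direction | 0.05 decides: r = 0.5 (r = 0.8 to 0) | 0.01 decides: r = 0.5 (r = 0.8 to 0) |
|---|---|---|---|
| All 14 | either | 34.8% (19.7-51.2%) | 9.3% (5.1-13.1%) |
| All 14 | benefit | 17.4% (9.9-29.8%) | 4.6% (2.6-6.8%) |
| CSHQ, 8 | either | 25.0% (15.8-33.7%) | 6.1% (3.9-7.7%) |
| CSHQ, 8 | benefit | 12.5% (7.9-18.3%) | 3.1% (1.9-3.9%) |
| ABC, 6 | either | 20.7% (13.9-26.5%) | 4.9% (3.3-5.9%) |
| ABC, 6 | benefit | 10.4% (6.9-14.1%) | 2.4% (1.7-3.0%) |

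The comparators for one two-sided 0.05 test are 5% in either direction and 2.5% for benefit.

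**Sensitivity to the form of the correlation.** With each total built as the sum of its subscales, correlation 0.5 within a scale and 0.3 between scales, the 14-score rates are 35.4% and 9.2% in either direction, and 18.0% and 4.7% for benefit. The result does not hinge on the equal-correlation model.

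**Sensitivity to the CSHQ count.** If the five blocks of the Appendix 3 form were the subdomains, the CSHQ would have 6 scores and the same rates as the ABC row. The total would be 12 scores. At r = 0.5 the same formula gives 31.9% and 8.3% in either direction, and 16.0% and 4.2% for benefit.

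**Effect of naming one total per scale.** Two totals, each at 0.05 with no further rule, give 8.4-9.8% in either direction (r = 0.7 to 0). Holm over the two totals (0.05/2 = 0.025, then 0.05) holds this at or below 5% in either direction. With no true effect, a false benefit is at most 2 x 0.0125 = 2.5%.

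**The case against.** The strongest reply is that section 9.2.1 does contain a multiplicity step. If it is enforced at 0.01, the scales taken one at a time are close to where they should be: ABC 4.9% and CSHQ 6.1% in either direction, and 2.4% and 3.1% for benefit against 2.5%. The 9% arises only when sleep and ABC are pooled into one family, and whether secondary outcomes for different objectives need joint control at 5% is a matter of judgement. The plan also says below 0.01, not 0.01 exactly, and 0.0083, 0.00625 and 0.0036 all satisfy that.

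Most of this stands. The plan has not fixed a wrong divisor; it has left the divisor, the family and the deciding level unstated. Nor can one say that the plan, followed exactly, gives 35%: that figure requires 0.05 to decide, which the text permits but does not require.

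Three stronger readings should also be set aside:
- A reader might infer that a trial with no effect would claim a secondary benefit up to 35% of the time. That rate counts results favouring sham as well. For benefit alone the rate is 17% at correlation 0.5, and it does not reach 35% even with independent scores (29.8%).
- A reader might infer that an ABC subdomain could rescue the primary objective. Sections 2.2 and A5.3 both label the ABC secondary.
- A reader might take 8 CSHQ scores as the plan's number. The documents do not fix the subdomains.

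What the objection does not remove is the absence of a deciding score for a stated hypothesis and the uncertainty over which level applies.

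**Conclusion.** The point holds as a defect in how the secondary claims are defined. Neither the sleep hypothesis nor the ABC outcome has a deciding score, neither depends on ATEC, and the Bonferroni step has no stated family or role.

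If 0.05 decides, the chance of a false benefit over 14 scores is about 17.4/2.5 = 7.0 times that of a single test at correlation 0.5. If 0.01 decides, it is about 4.6/2.5 = 1.8 times over all 14 scores, and near 1 within either scale. The serious exposure is therefore that 0.05 may decide.

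These sizes rest on no true effect on any score, the assumed correlation, 8 CSHQ scores, and a single final analysis. They leave out the interim tests in A5.3, for which no adjustment is stated and which could only raise the rates if a claim could be made at either look. These are secondary claims, so the change is one that should be made rather than one on which the trial's validity depends.

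**What to change.** In sections 2.2, 2.3 and 9.2.1:

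1. Name CSHQ total as the only deciding score for the sleep hypothesis and ABC total as the only deciding score for the ABC outcome, both on the between-arm comparison.
2. Label all CSHQ and ABC subdomain scores exploratory, list the CSHQ subdomains, and report them as estimates with 95% confidence intervals and no significance claim.
3. For these outcomes, replace the undefined < 0.01 step with a stated rule over the two totals, such as Holm at two-sided 0.05 (0.025, then 0.05).

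Testing the totals only after a significant ATEC result is an option, but it needs the sponsor first to name a single deciding ATEC comparison, which section 2.2 does not do. Any fixed order between ABC and CSHQ should be justified by the sponsor. In particular, nothing in the documents supports making the ABC, which sits under the social-functioning objective, wait on the sleep result.

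The cost is wording only, with no new data or participants. Subdomain results become descriptive. If the ATEC gate is adopted, no confirmatory sleep or ABC claim is possible when ATEC fails. In return, each total is tested at 0.025 or 0.05 rather than below 0.01.
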